### Process variables

#### Intervention fidelity

Delivery of the intervention is assessed by the GHS, data includes;
commencement, the number, length, and timing of coaching calls and
achievement of identified goals.

#### Concomitant treatments

Participants were asked to record separately all medication and health care
services used for the back or knee pain, for each trial respectively, at
baseline, and weeks 6 and 26 post-randomisation. Information for each
additional treatment was provided as free text often using variable
terminology. These will be aggregated using a common terminology.
Medications will be coded using the Anatomical Therapeutic Chemical
Classification System at the third level. Other health services will be
coded according to common provider types, for example specialist, hospital
or emergency department presentation or admission, physical therapy,
chiropractic, massage therapy, other allied health, alternative medicine,
and other.

#### Safety

Participants were monitored for adverse events throughout the intervention
period. All adverse events (AE), that is, any new medical conditions or an
exacerbation of another existing condition, were recorded at 6 and 26 weeks.
All AEs will be described for each group.

### Design issues

#### General design

These trials were parallel group RCTs, established as part of a cohort
multiple RCT. Patients waiting for an outpatient orthopaedic consultation at
a public tertiary referral hospital within NSW were sent an information
letter to invite participation in the cohort (telephone survey) and again at
12-months follow-up. At 12-month follow-up patients consenting to the
telephone survey were screened for eligibility for the RCT by a trained
interviewer and invited to participate if eligible for the study.

#### Treatment allocation

Eligible patients were randomised in a 1:1 allocation ratio, to either
receive the weight management and healthy lifestyle intervention at that
time (intervention group) or remain as part of the cohort and be told they
will be offered clinical services in 6 months (control group). The
randomisation schedule was generated a priori by an independent statistician
using SAS 9.3 through the SURVEYSELECT procedure. To randomise patients, a
trained interviewer opened a sealed opaque envelope containing group
allocation. A staff member not involved in the study prepared the
envelopes.

#### Sample size

The sample size for both trials was calculated using Stata sample size
calculator.

For trial one a standard deviation of 2.3, a two-sided alpha of 0.025 (to
account for two outcomes of interest, the primary outcome (pain) and the key
secondary outcome (weight)^22^ and allowing for 15% loss to follow-up was used. A sample size of 80
participants per group (n=160) has 90% power to detect a clinically
meaningful difference of 1.5 points in pain intensity (pain NRS) between
intervention and control groups^23^. This sample also provides power 80% to detect a 6% reduction in
weight in the underlying sampling population, based on evidence from other
musculoskeletal conditions this is hypothesised to lead to a clinically
meaningful reduction in pain^23^.

For trial two a standard deviation of 2.7, a two-sided alpha of 0.025 (to
account for two outcomes of interest, the primary outcome (pain) and the key
secondary outcome (weight)^22^ and allowing for 15% loss to follow up, a sample of 60 participants
per group will provide 90% power to detect a clinically meaningful
difference of 2 points in pain intensity (pain NRS) scores between
intervention and control groups at 26 weeks. This sample also provides 80%
power to detect a 6% weight reduction which is hypothesised to be lead to a
clinically meaningful reduction in pain^23^.

In these calculations the increase in statistical power conferred by reducing
error variance through repeated outcome measures over time and the
correlations among repeated measures have been conservatively ignored.

#### Data collection and follow up

The different stages of data collection and follow-up for secondary outcomes
are summarised in table one. The primary outcome, pain intensity score, was
collected at baseline, week 2, 6, 10, 14, 18, 22 and at 26 weeks. Baseline
assessment was conducted prior to randomisation.

#### Interim analysis

No interim analysis was conducted.

## Statistical analysis

### Trial profile

Flow of the patients through the study will be displayed in a Consolidated
Standards of Reporting Trials (CONSORT) diagram for each trial. We will report
the number of screened patients who met study inclusion criteria, reasons for
exclusion of non-included patients, the number of participants randomised per
group, and the number who completed follow-up, as shown in Figures 1A and 1B.

**Figure 1A gf01:**
[figure not shown]
Progress of participants through trial one (low back pain).

**Figure 1B gf02:**
[figure not shown]
Progress of participants through trial two (knee
osteoarthritis).

### Data integrity

Trial data integrity will be monitored by regularly scrutinising data files for
data omissions and errors. Manually entered data (i.e. data not recorded
directly by the participant) will be double entered and the source of any
inconsistencies will be explored and resolved in consultation with the lead
investigator (CW).

### Analysis principles

Primary analyses will be conducted independently by an independent statistician
who is blinded to group status.

Analyses will be conducted using SAS V9.4 (SAS Institute, Cary, North Carolina,
USA). Intention-to-treat (ITT) (analysed as randomised) will be utilised. All
statistical tests will be two-tailed. Treatment effect for the primary and
secondary outcomes will be considered significant if *p*≤0.025
and *p*≤0.01, respectively.

Summaries of continuous variables that are symmetrically distributed will be
presented as means and standard deviations (SD) or medians and inter-quartiles
for skewed data, whereas categorical variables will be presented as frequencies
and percentages. Large count variables will be reported as medians and
interquartile ranges, low counts (max count <5) will be presented as
frequencies and percentages.

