#### Secondary outcomes

The secondary outcomes include:

•Physical disability and function, measured in trial one using the
Roland Morris Disability Questionnaire (RMDQ)^9^ 0-24 scale and measured in trial two using the Western
Ontario and McMaster Universities Osteoarthritis Index (WOMAC) 0-96
scale^10^;•Self-reported weight (kg);•Objective weight (kg) measured to the nearest 0.1kg by a trained
research assistant using International Society for the Advancement
of Kinanthropometry (ISAK) procedures^11^;•BMI calculated as weight /height squared (kg/m^2^)^12^;•Waist circumference measured by a trained research assistant using
ISAK procedures taken at the level of the narrowest point between
the inferior rib border and the iliac crest using a flexible tape
measure to the nearest 0.1 cm^11^;•Quality of life, measured using the physical and mental health
component scores from the 12-item Short Form Health Survey version 2
(SF12.v2)^7^;•Global perceived change in symptoms, measured using the Global
Perceived Effect (GPE) scale (-5 ‘vastly worse’ to 5 ‘completely
recovered’)^13^;•Emotional distress, measured using the Depression Anxiety Stress
Scale-21 (DASS-21) 0-63 scale^14^;•Sleep quality, measured using item 6 from the Pittsburgh Sleep
Quality Index (response options: very bad, fairly bad, fairly good,
very good)^15^;•Physical activity, measured using the Active Australia Survey^16^, reported as the average minutes spent participating in
moderate-to-vigorous physical activity (MVPA) per week;•Diet, measured using a short food frequency questionnaire (FFQ)^17^, reported as serves of fruit (0-1, 2 or more), serves of
vegetables (0-2, 3-4, 5 or more), serves of discretionary foods
including processed meats, salty snacks, takeaway meals, sweet or
savoury snacks, confectionary and sugar sweetened beverages (more
than once per week, once per week or less);•Alcohol consumption measured using the Alcohol Use Disorders
Identification Test (AUDIT) 0-12 scale^18^;•Smoking prevalence (have you smoked any tobacco in the last 4 weeks?
(this can include cigarettes, roll your own, pipes, cigars or any
other tobacco products))^19^;•Attitudes and beliefs, measured using the Survey of Pain Attitudes
(SOPA)^20^; and the physical component of the Fear Avoidance Beliefs
Questionnaire (FABQ) 0-24 scale^21^; and•Health care utilisation for each trial respectively, including back
or knee pain medication use (name), type of health service utilised

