### Primary analysis

To examine between-group differences in the primary outcome (AUC – based on pain
intensity score) we will use an independent sample Students t-test. The primary
analysis will not adjust for known prognostic variables as covariates, but
results adjusting for these will be presented as a sensitivity analysis (see
below). Separate models will be estimated for each imputed dataset and the means
and standard errors will be combined using Rubin’s method^25^. We will assess other model assumptions (homoscedasticity, normality)
through inspecting appropriate residual plots, where serious violations are
observed we will apply a rank-inverse normal transformation to the pain
intensity score values. Dummy coded variables representing group allocation will
be used to ensure blinding of the analyses. See Table 3 for details.

**Table 3 t03:** Analyses of primary outcome.

**Analysis**	**Outcome**	**Intervention**	**Control**	**Difference**
Primary (ITT Multiple Imputation)	Area under the pain intensity curve (AUC)	mean(95%CI)	mean(95%CI)	mean(95%CI)
Sensitivity	Adjusted AUC*	mean(95%CI)	mean(95%CI)	mean(95%CI)
Secondary	Pain intensity score			
	Baseline	mean(SD)	mean(SD)	
	Week 2,	mean(SD)	mean(SD)	
	Week 6	mean(SD)	mean(SD)	
	Week 10	mean(SD)	mean(SD)	
	Week 14	mean(SD)	mean(SD)	
	Week 18	mean(SD)	mean(SD)	
	Week 22	mean(SD)	mean(SD)	
	Week 26	mean(SD)	mean(SD)	
	Weekly trend	mean(95%CI)	mean(95%CI)	mean(95%CI)

* Adjusted for baseline pain and duration, waiting time, previous
surgery; BMI: physical activity and dietary intake; ITT: Intention
to treat.

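### The stated 80% power for weight, the key secondary outcome, does not match its planned test: the design uses two-sided alpha 0.025, the analysis rule p≤0.01

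*Protocol article*

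**What the plan says.** The Sample size section of the protocol article gives both trials "a two-sided alpha of 0.025 (to account for two outcomes of interest, the primary outcome (pain) and the key secondary outcome (weight"), with 15% loss to follow-up. For trial one (80 per group) it adds: "This sample also provides power 80% to detect a 6% reduction in weight". For trial two (60 per group) it likewise claims 80% "power to detect a 6% weight reduction". Neither weight sentence repeats an alpha or gives a standard deviation.

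Under Analysis principles, "statistical tests will be two-tailed", and effects on the primary and "secondary outcomes will be considered significant if *p*≤0.025 and *p*≤0.01, respectively".

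The Secondary outcomes section lists two weight measures: "Self-reported weight (kg") and objective weight in kg. The Secondary analysis section assigns objective weight to a t-test at 26 weeks. Self-reported weight, collected at weeks 0, 6 and 26 (Table 2), falls under the mixed models for repeated outcomes. The label of key secondary outcome appears only in the Sample size section, which does not say which weight measure it means.

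**The concern.** The design alpha is set at 0.025 expressly because weight is considered alongside pain, and a power figure for weight follows in the same paragraph. The natural reading is that weight was meant to be tested at 0.025. The analysis rule treats weight like any other secondary outcome and holds it to 0.01. A stricter threshold with the same sample gives lower power, so a reader who relies on the 80% would overestimate the chance of detecting the planned weight effect.

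This matters for interpretation. The Sample size section presents weight loss of this size as the hypothesised route to less pain. If weight misses 0.01, the reader needs to know how likely that was under the planned effect. The article presents itself as the pre-determined analysis plan, and both figures are printed in it, so this is a conflict in the text and not a detail left to another document.

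**Working it through.** **Inputs.** From Sample size: two-sided alpha 0.025; weight power 80%; 80 and 60 per group; 15% loss, leaving 80 × 0.85 = 68 and 60 × 0.85 = 51 evaluable per group; pain SD 2.3 and 2.7; pain differences 1.5 and 2 points at 90% power. From Analysis principles: two-sided 0.01 for secondary outcomes.

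**1. Can the 80% be reproduced?** No. The article gives neither an SD nor a baseline mean for weight. The check therefore takes the 80% as given and asks what the change of threshold does to it.

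**2. Power at 0.01 if the 80% was calculated at 0.025.** The standardised signal that gives 80% power is z(0.9875) + z(0.80) = 2.2414 + 0.8416 = 3.0830. The critical value at two-sided 0.01 is 2.5758. Power = Φ(3.0830 − 2.5758) = Φ(0.507) = 69.4%.

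With the noncentral t distribution, taking for each group size the standardised effect that gives 80% at 0.025:

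| Per group | Standardised effect | Power at 0.01 |
|---|---|---|
| 80 | 0.491 | 69.1% |
| 68 | 0.534 | 69.1% |
| 60 | 0.569 | 69.0% |
| 51 | 0.618 | 69.0% |

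The chance of missing the effect rises from 20% to about 31%, and the result hardly depends on the group size.

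**3. Power at 0.01 if the 80% was calculated at another alpha.** This is an assumption, because the weight sentences state no alpha.

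- At 0.05: 1.9600 + 0.8416 = 2.8016; Φ(2.8016 − 2.5758) = Φ(0.226) = 58.9%.
- At 0.0125: 2.4977 + 0.8416 = 3.3393; Φ(3.3393 − 2.5758) = Φ(0.764) = 77.7%.
- At 0.01 there would be no loss, but nothing in the text says that 0.01 was used.

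**4. Do the pain figures confirm 0.025 as the working alpha?** The formula is n = 2(z_α + z_β)²(SD/difference)² per group, rounded up, then divided by 0.85.

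- Trial one at 0.025: 2 × (2.2414 + 1.2816)² × (2.3/1.5)² = 58.4, so 59, or 70 per group after loss. The article states 80.
- Trial one at 0.0125: 2 × (2.4977 + 1.2816)² × (2.3/1.5)² = 67.2, so 68, or 80 per group after loss. This equals the stated figure.
- Trial two at 0.025: 2 × (2.2414 + 1.2816)² × (2.7/2)² = 45.2, so 46, or 55 per group after loss. At 0.0125 it is 52.1, so 53, or 63 per group. The stated 60 lies between.

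The stated sizes exceed what pain needs at 0.025, so pain is not underpowered. They do not confirm that 0.025 was the alpha entered, which is why step 3 is needed.

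**5. Sample needed to keep 80% at 0.01.** The ratio to the 0.025 design is ((2.5758 + 0.8416)/3.0830)² = 1.229. That is 80 × 1.229 = 98.3, so 99 per group in trial one, and 60 × 1.229 = 73.7, so 74 in trial two. The Introduction says recruitment closed in October 2015, so the sample cannot be enlarged.

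**The case against.** The strongest reply is that 0.01 is a sensible precaution against a long list of secondary outcomes and that applying it to weight only makes the trials stricter. That stands as far as type I error goes: weight is not tested too liberally and the pain test is unaffected. It does not rescue the power statement, which is printed for a design at 0.025.

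A second reply is that 69% is not established, since the weight sentences name no alpha and trial one's size fits 0.0125 better than 0.025. This also stands, so 69% is the value on the article's own stated alpha and not a fact about the calculation. In addition, the Sample size section says that gains from repeated measures were ignored. For self-reported weight in a mixed model, realised power could therefore differ from any of these figures.

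Some stronger readings are tempting but not supported:

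- A reader might infer that a weight p-value of 0.02 has two conflicting verdicts. It has one. The Sample size section gives planning inputs, and the only decision rule is in Analysis principles, under which 0.02 is not significant.
- A reader might infer that 0.025 − 0.01 = 0.015 of alpha is wasted. That looks at pain and weight alone, whereas the 0.01 rule covers the whole secondary list.
- A reader might infer that the 95% intervals in the results tables are an error. Significance is defined by p-values, and showing 95% intervals beside a stricter threshold is a reporting choice.
- A reader might infer that objective weight at 26 weeks is the designed key secondary outcome. The article says only weight.

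**Conclusion.** The concern holds as an inconsistency between the planning alpha for weight and the threshold at which weight will be tested. On the stated 0.025, the claimed 80% becomes about 69% in both trials. The plausible range is about 59% (calculated at 0.05) to about 78% (calculated at 0.0125). All of these take the 80% itself as correct, which the article does not allow anyone to verify.

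The consequence is limited to how a secondary result is read. The direction is conservative for type I error, and the primary conclusion on pain does not depend on it. It should be fixed before analysis, but it does not threaten the trials' validity.

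**What to change.** Before any unblinded analysis, reconcile Sample size with Analysis principles in one of two ways:

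1. Keep p≤0.01 for weight and restate its power: about 69% if the 80% was calculated at 0.025, otherwise the figure for the alpha actually used.
2. State that the key weight outcome is tested at p≤0.025 and that 0.01 applies to the other secondary outcomes.

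In either case, say whether the key outcome is self-reported or objective weight, and give the alpha and SD behind the 80%.

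Both options need wording only. The first leaves the decision rule as signed. The second relaxes a threshold that, according to the Introduction, the investigators approved in May 2016, the month in which follow-up ended. It should therefore be recorded as a dated change, made while still blind to group.

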## Objectives

The primary objective of both trials is to establish if:

Trial one: pain education and referral to a telephone-based weight management and
healthy lifestyle intervention improves pain intensity in patients with *low
back pain*, who are overweight or obese, compared to usual care.

Trial two: referral to a telephone-based weight management and healthy lifestyle
intervention improves pain intensity in patients with *knee
osteoarthritis*, who are overweight or obese compared to usual care.

Secondary aims of the two trials is to establish if the telephone interventions lead
to reductions in disability, weight, BMI, waist circumference, alcohol consumption,
and smoking prevalence, and improvement in quality of life, emotional distress,
sleep quality, physical activity, diet, pain attitudes and beliefs, perceived change
in condition and change in health care and medication use.

A separate analysis plan will be detailed for health economic analyses and is not
included in this manuscript.

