### Secondary analysis

Between group differences in the trajectory of pain intensities over the
follow-up period will be examined using growth curve modelling. Hierarchical
linear models will be used, with fixed effects for treatment group, time, and
the interaction between the two. The model will include random subject-level
intercepts and slopes. A linear growth trend will initially be assumed, and if
not appropriate different functional forms for the trend will be applied (for
example the square root transformation). If an appropriate functional form
cannot be determined a flexible piecewise linear model will be used^26^. We will also investigate treatment effect heterogeneity that may exist
in latent subgroups of participants through growth mixture models^27^. In these models a number of latent classes are specified that model the
potential for participants to have different trajectory types, the functional
forms identified from the previous growth curve analyses will inform the
functional forms for this analysis. The model will include the following random
effects that are all conditional trajectory class membership: intercept linear
slope and quadratic slope. The random effects are influenced by the treatment
group, so there will potentially be 3 lots of treatment effects (for each random
effect) for each latent class.

Longitudinal generalised linear mixed models will be used to assess treatment
effect on post randomisation secondary outcome measurements with random
intercepts for individuals to account for correlation of repeated measures and
an appropriate link function dependent on the type and distribution of the data.
We will compare the adjusted mean change (continuous variables) or relative
risks (dichotomous variables) in outcome from baseline to each time point
between the treatment and control groups. A binomial distribution family (with
log link) will be used for dichotomous outcomes (sleep quality, smoking
prevalence), and a Poisson or negative-binomial distribution family (with a log
link function) will be used for count outcomes (health care utilisation) based
on assessment of data dispersion. T-tests will be used to test between group
differences in variables collected only at 26 weeks (objective weight, BMI,
waist circumference). See Table 4 for
details.

**Table 4 t04:** Secondary outcomes.

**Outcome**	**Intervention**	**Control**	**Intervention - control**
Disability and function (Trial 1: RMDQ / Trial 2: WOMAC)			

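### A flat p≤0.01 for all 22 secondary outcomes has no deciding contrast and no supportive label, and it drops the 0.025 shared by pain and weight in the sample size

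*Protocol article*

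**What the plan says.** All places are in the protocol article.

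- **Threshold.** Under Analysis principles, tests are two-sided. A treatment effect counts as significant at p≤0.025 for the primary outcome "and *p*≤0.01, respectively" for secondary outcomes. No derivation of 0.01 is given and no secondary outcome is exempted.
- **Aims.** The Objectives section introduces the secondary outcomes with "Secondary aims of the two trials is to establish if the telephone interventions lead" to reductions or improvements in a long list of measures.
- **Contrasts.** The Secondary analysis section compares the groups on change "in outcome from baseline to each time point". Table 4 adds an Overall row for every outcome with repeated follow-up, and also for two outcomes with a single follow-up.
- **Hierarchy in the design.** The Sample size section uses a two-sided alpha of 0.025 in both trials, to "account for two outcomes of interest, the primary outcome (pain) and the key" secondary outcome, weight. It states 80% power for a 6% weight reduction.
- **Latent classes.** A growth mixture model of pain is also planned, "so there will potentially be 3 lots of treatment effects (for each random" effect) in each class. No threshold or status is given for these effects.

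**The concern.** The plan fixes a rule for declaring secondary effects significant but leaves open what the rule applies to. For most outcomes three contrasts are available. An outcome that passes 0.01 at week 6 and not at week 26, or the reverse, could be called positive or negative, and the text does not settle which. A threshold of 0.01 looks strict, but it is applied separately to 22 outcomes with nothing said about how the results are to be read together.

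The second problem is an inconsistency. The one ordering in the design, pain first and weight as key secondary outcome, is not carried into the significance rule. Read literally, weight is sized at 0.025 and judged at 0.01. The Secondary outcomes section lists self-reported weight and objective weight separately, and the Sample size section does not say which is key.

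At stake is what each trial may conclude on weight, lifestyle, quality of life and health-care use. The primary comparison of pain area under the curve is not touched.

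**Working it through.** **1. The plan's own figure.** Two outcomes sharing 0.05 gives 0.05 / 2 = 0.025, as stated in the Sample size section. The 0.01 cannot be reproduced, because no family size or error rate is stated for it. By Bonferroni, 0.01 holds 5% over 0.05 / 0.01 = 5 tests.

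**2. Count from Table 4.**

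| Outcomes | Number | Distinct post-baseline contrasts |
|---|---|---|
| Week 6, week 26 and Overall | 16 | 16 × 3 = 48 |
| Week 26 and Overall, one follow-up only (DASS-21, FABQ) | 2 | 2 |
| Week 26 only (objective weight, waist, orthopaedic consultation, surgery) | 4 | 4 |
| Total | 22 | 54 |

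Counting the Overall rows of DASS-21 and FABQ separately gives 56. BMI is counted at three contrasts as in Table 4, although the Secondary analysis text lists it among variables collected only at 26 weeks. Counting it once gives 54 − 2 = 52. None of these choices changes the conclusion.

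**3. One contrast per outcome, no effect anywhere.** If the tests were independent, the chance of at least one p≤0.01 is 1 − 0.99^22 = 19.8%. The article gives no correlations, so they are assumed. Simulating correlated normal statistics, two-sided 0.01:

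| Between-outcome correlation | Chance of at least one false claim, 22 tests |
|---|---|
| 0 | about 20% |
| 0.3 | about 17% |
| 0.5 | about 13% |
| 0.7 | about 8.5% |

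**4. All contrasts counted.** Week 6 and week 26 are assumed to correlate 0.7 within an outcome, and Overall is taken as their average. Overall then correlates (1 + 0.7) / √(2 + 2 × 0.7) = 0.92 with each week, so it adds little. The simulated chance is about 31% at between-outcome correlation 0, about 20% at 0.5, and 11–13% at 0.7. At 0.7 the result depends on whether the correlation between different outcomes is as strong across time points as within one (11%) or weaker (13%).

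**5. Weight at the two thresholds.** This step takes the stated 80% power to be at the stated two-sided 0.025. The standardised effect is then z(0.9875) + z(0.80) = 2.241 + 0.842 = 3.083. At two-sided 0.01 the critical value is z(0.995) = 2.576. Power is Φ(3.083 − 2.576) = Φ(0.507) = 0.69. The weight SD is not given, and this comparison does not need it.

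**The case against.** The case against is substantial.

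- **Each trial has one primary contrast, and the rest are labelled secondary and held to a stricter threshold.** True. The article never promises 5% family-wise error over the secondary outcomes. The 0.05 behind the sample size was allotted to pain and weight only, so it is not a budget that the others exceed. Whether to control error formally across secondary outcomes is a matter on which statisticians differ.
- **A reader might infer that a false secondary claim is likely.** The figures do not support that. No scenario above reaches 50% for one trial, and the upper ends assume uncorrelated outcomes. That is implausible for a set containing self-reported weight, objective weight, waist and BMI.
- **A reader might infer that the plan has no hierarchy.** It has one: pain is primary and weight is key secondary. What is missing is its use in the significance rule.
- **Table 4 shows estimates with confidence intervals and no p-values, so treating every row as a claim is a reading.** Also fair. That is why the one-contrast figure comes first. But the text does not exclude the other reading.
- **The growth mixture model is worded as an investigation of possible heterogeneity.** Agreed. The number of classes and the threshold are not given, so no added error rate can be attributed to it from the article. Only a label is needed.
- **A reader might fear that a chance secondary finding will be presented as the trial's benefit if pain is null.** Tables 3 and 4 provide for reporting all results, so the documents do not show this.

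What remains is a stated significance rule with no deciding contrast and no stated status for the outcomes it covers, and a direct mismatch on weight. Neither is a detail left to a fuller document, because the article presents this rule as its pre-determined analysis plan.

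**Conclusion.** The concern holds in a limited form. As written, the flat 0.01 gives each trial a chance of about 8–20% of at least one false secondary claim with one contrast per outcome, and about 11–31% if week 6, week 26 and Overall all count. These figures assume no effect on any secondary outcome, between-outcome correlations of 0 to 0.7, within-outcome correlation of 0.7, and Overall as the average of the two weeks. This inflation is material, but it does not make a false claim probable.

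The firmer finding needs no correlation assumption. Weight shares the 0.025 with pain in the sample size and is judged at 0.01 in the analysis, where 80% power becomes about 69%. The two sections must be reconciled. The point should be corrected because it changes what may be concluded from the secondary outcomes; it does not threaten the primary analysis.

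**What to change.** 1. In Analysis principles, exempt the key secondary outcome and test it at the 0.025 used for sizing, or keep 0.01 and restate its power. State whether weight means self-reported or objective weight.
2. Name one deciding contrast for each remaining secondary outcome, for example week 26, and make the other contrasts descriptive. Settle whether BMI is analysed at week 26 only or at all its Table 4 time points.
3. Label the remaining secondary outcomes and the latent-class effects supportive or exploratory. Report them as estimates with confidence intervals, without declaring significance.
4. Soften the wording of the secondary aims in Objectives to match.

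A Holm procedure over the deciding contrasts is an option, not a requirement.

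The cost is wording in three sections and the notes to Table 4, with no new data or models. The downside is that individual secondary results other than weight could no longer be called significant on their own. If the analyses scheduled for June 2016 have already been run, the labels can still govern how the results are reported, with the date of the clarification given.
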